## Abstract

**Background:**

A large proportion of patients with spinal cord injury (SCI) regain ambulatory function. However, during the first 3 months most of the patients are not able to walk unsupported. To enable ambulatory training at such an early stage the body weight is partially relieved and the leg movements are assisted by two therapists. A more recent approach is the application of robotic based assistance which allows for longer training duration. From motor learning science and studies including patients with stroke, it is known that training effects depend on the duration of the training. Longer trainings result in a better walking function. The aim of the present study is to evaluate if prolonged robot assisted walking training leads to a better walking outcome in patients with incomplete SCI and whether such training is feasible or has undesirable effects.

**Methods/Design:**

Patients from multiple sites with a subacute incomplete SCI and who are not able to walk independently will be randomized to either standard training (3-5 sessions per week, session duration maximum 25 minutes) or an intensive training (3-5 sessions per week, session duration minimum 50 minutes). After 8 weeks of training and 4 months later the walking ability, the occurrence of adverse events and the perceived rate of exertion as well as the patients' impression of change will be compared between groups.

**Trial registration:**

This study is registered at clinicaltrials.gov, identifier: NCT01147185.

## Background

The general prognosis for regaining ambulatory function after a traumatic SCI ranges from 3% in initially complete SCI patients (according to the Standard Classification of the American Spinal Injury Association ASIA A [1]) to 95% in very incomplete lesions (ASIA D) [2]. It is reported that for patients with a motor complete and sensory incomplete SCI (ASIA B) the chance to become ambulatory is 50%. Those subjects with preserved algesia seem to recover to about the same extent as motor incomplete SCI subjects [3].

The basis for locomotor training after acute spinal cord injury (SCI) in humans is provided by animal experiments which showed training induced plasticity of spinal locomotor centers [4]. In humans with a clinically complete spinal injury walking-like EMG activity can be elicited when subjects perform bodyweight supported and assisted stepping on a moving treadmill [5]. In SCI rehabilitation body weight supported treadmill training (BWSTT) has become established within the last 2 decades. In severely affected SCI subjects movements of the patient legs have to be manually assisted by two therapists. In some cases a third therapist might be needed to stabilize the pelvis. The shortcoming of such manual assisted BWSTT is that it is very exhaustive for the therapists and hence only allows for limited training time. In addition the application of movement assistance requires extra skills to maintain coordination between the two legs. In order to provide longer training sessions with a consistent movement pattern robotic gait devices were developed. These driven gait orthoses (DGO) become successively more established to treat individuals with a locomotor dysfunction such as incomplete SCI, stroke or traumatic brain injury [6]. A widely used DGO is the Lokomat (Hocoma AG, Volketswil, Switzerland, Figure 1) [7]. It has been shown that locomotor training with the Lokomat is feasible and that patients with a chronic incomplete SCI could improve gait speed and endurance as a response to an intensive training which lasted 8 weeks [8].

**Figure 1 F1:**
[figure not shown]
**The Lokomat is an actuated robotic exoskeleton for the training of ambulatory function on a moving treadmill**. The patient is secured by an overhead suspension system which partially reliefs the body weight. Position sensors and force transducers are used to monitor the efforts of the patient (Picture by courtesy of Hocoma AG).

Patients with mild para- or tetraparesis become ambulatory within days or weeks without being trained using special forms of therapy e.g. BWSTT or Lokomat. In contrast, SCI subjects presenting with an incomplete but severe spinal paresis (i.e. ASIA B and C) are referred to an intensive and specific locomotor training by the Lokomat. So far this algorithm is based on expert consensus [9].

The strategy of rehabilitation after SCI or stroke is based on the principles of motor learning. Important characteristics of exercises have been identified. Beside task-specificity, task-variability, feedback or contextual interference the amount of exercise seems to be a key element [10,11]. The improvement of motor performance within rehabilitation may be due to true recovery or compensation [12]. Nevertheless, the above mentioned principles are valid regardless the underlying mechanism [11].

A meta analysis including studies of patients with stroke showed that augmented exercise therapy had a favorable effect on activities of daily living [13] and longer training duration was correlated with improved walking performance (positive dose-response relationship) [14]. One of the advantages of robotic devices like the Lokomat is the ability to prolong time for locomotor training compared to manually assisted training [15]. Yet it is not clear whether longer training duration results in an improved outcome or if certain endpoints in terms of walking capacity can be achieved within a shorter period of time.

The aim of the present study is therefore to evaluate whether SCI patients with severe sensory-motor deficit after acute traumatic SCI (ASIA B and C) profit from prolonged Lokomat training compared to patients who undergo the usual training paradigm. The hypothesis is that patients with a severe but incomplete SCI who undergo a prolonged Lokomat training achieve higher grades of walking ability compared to their counterparts who complete the training as suggested by experts.

The secondary aim is to evaluate how feasible prolonged locomotor training time is, i.e. whether there is an association between training intensity and adverse events e.g. increased spasticity or pain.

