### Intervention

The locomotor training with the Lokomat device should start within approximately 30 days but not later than 60 days after the SCI. The observation period of the training for this study lasts 8 weeks. For the initial 5 trainings there are no defined specifications. These trainings serve to optimize the setup and for the patients to familiarize with the robotic locomotor training device. During subsequent trainings following guideline will be adopted to adjust the training to the actual capacity: body weight unloading will be reduced to the least tolerated amount (no knee buckling or toe dragging). The walking speed will be set within the range of 1.6 to 3.1 km/h and the guidance force in the range from 100% (full assistance) to minimum tolerated. The training session will be shaped in the following way: 3 min walking without specification (warm-up period) after that, every 3^rd ^minute either speed, visual feedback or guidance force will be changed. This will avoid that the training becomes monotone and lacks challenge.

Patients who will be assigned to the intervention group receive one or two Lokomat trainings per day on 3-5 days per week. The Lokomat walking time per day should not be shorter than 50 min.

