### Outcome

Outcome data will be assessed in the respective centers by therapists and medical doctors. Hereafter the data will be sent anonymously to the PI for analyses. Due to the characteristic of this study neither the therapists nor the assessors nor the patients can reliably be blinded regarding the group allocation. The principal investigator (PI) who is the first author of this report (MW) and will be involved in the analyses will not be aware of the respective intervention.

In order to describe the characteristics of the included subjects, demographic and clinical data will be assessed. The primary outcome is the self selected walking speed using the Ten Meter Walking Test (TMWT) [24]. It will be assessed at baseline, bi-weekly during training, and at the six months follow-up. In addition the following items will be assessed at baseline, bi-weekly during training, and after six months: the Walking index for spinal cord injury -WISCI [17] (an ordinal scaled index for the assessment of walking capabilities with 21 categories. Zero represents that the patient is not able to stand or walk, the maximum of 20 means that the patient can walk without bracing, walking aids or personal assistance), the maximum walking speed, the ASIA classification [1], the detailed Spinal Cord Independence Measure-SCIM [25], the modified Ashworth scale-MAS [26] of hip and knee joints, and the Penn spasm frequency scale [27]. During the training period the mechanical stiffness and the maximum voluntary torque of the legs as well as the cooperation of the patient during the training will be assessed bi-weekly using the force transducers of the robotic training device. For every training the distance walked, walking speed, walking time and body weight unloading, the rate of perceived exertion as well as the occurrence of any events (e.g. skin breakdown or joint stress or scheduling problems) will be assessed. At the end of the training period, i.e. after 8 weeks the patients subjective impression about the success of the training will be assessed using the Patients' Global Impression of Change Scale-PGIC [28].

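### Pain is one of two harms named in the secondary aim, but unlike spasticity it has no dedicated, baseline-anchored measure in the assessment list

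*Protocol article*

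**What the plan says.** The Background closes with a secondary aim on the feasibility of longer training. It is put as a question of "whether there is an association between training intensity and adverse events e.g. increased spasticity or pain".

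The Outcome section then lists the assessments.

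- **Spasticity:** "the modified Ashworth scale-MAS [26] of hip and knee joints, and the Penn spasm frequency scale", at baseline, bi-weekly during training and after six months. The robotic device also records "the mechanical stiffness and the maximum voluntary torque of the legs" bi-weekly in the training period.
- **Dose received:** "For every training the distance walked, walking speed, walking time and body weight unloading".
- **Tolerance and events:** also at every training, "the occurrence of any events (e.g. skin breakdown or joint stress or scheduling problems) will be assessed", together with perceived exertion.
- **Patient's view of success:** a global impression of change at the end of the 8 weeks.

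The Methods/Design paragraph of the Abstract states the comparison: "the occurrence of adverse events and the perceived rate of exertion as well as the patients' impression of change will be compared between groups".

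Pain appears in one other place, the Subjects section, where chronic pain is among the pre-existing conditions that exclude a patient. It is not an outcome there.

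**The concern.** Any increase in pain with longer training has to be judged against the pain each patient had at the start. The article plans this for spasticity and not for pain.

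Excluding chronic pre-existing pain does not make the baseline zero. Patients enter within weeks of a traumatic injury and may have pain from it. A pain entry during training could then reflect the injury, the training or both.

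Reporting is the second difficulty. The Outcome section concedes that therapists, assessors and patients cannot reliably be blinded. A subjective symptom noted only when someone volunteers it can be noted more readily in one arm than in the other. A standard question put to everyone at fixed times does not remove the lack of blinding. It does remove differences in whether and how often pain is asked about.

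What is at stake is one part of the safety and tolerability answer. If pain is not recorded prospectively, no later analysis can recover it.

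**Working it through.** The plan gives no figure on this point, so the check sets the aim against the assessment list.

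**Step 1. Named harms against listed measures**

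| Feature | Spasticity | Pain |
|---|---|---|
| Named in the secondary aim | yes | yes |
| Dedicated clinical scale | two (modified Ashworth, Penn) | none listed |
| Device measure | stiffness | none |
| Baseline value | yes | none |
| Repeated at fixed times in training | yes, bi-weekly | none |
| Six-month value | yes | none |
| Open event record | possible | possible, not among its examples |

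**Step 2. Other listed items.** These are walking speed (self-selected and maximum), the walking index, the ASIA classification, the independence measure, device torque and cooperation, per-training dose, perceived exertion, events, and global impression of change. The article describes none of them as measuring pain.

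**Step 3. What the event record can supply.** The item reads "the rate of perceived exertion as well as the occurrence of any events" and is tied to each training. It therefore starts after baseline and stops when training stops. Its examples are skin breakdown, joint stress and scheduling problems. No severity grade is mentioned.

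**Step 4. The trial's sample size, used below to size the fix.** The Subjects section assumes a difference of 0.0418 m/s, SD 0.05 m/s, power 0.8 and significance level 0.05. The standardised difference is 0.0418 / 0.05 = 0.836. Two-sided, by the normal approximation, n = 2 × (1.960 + 0.842)² / 0.836² = 22.5, so 23 per group, as stated. The point about pain does not depend on this figure.

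**Step 5. Burden of a pain rating on the spasticity schedule.** Reading bi-weekly as every two weeks (an assumption), 8 weeks give 8 / 2 = 4 visits. With baseline and six months that is 1 + 4 + 1 = 6 ratings per patient, and 46 × 6 = 276 in the trial. If bi-weekly means twice a week, it is 1 + 16 + 1 = 18 per patient, or 46 × 18 = 828. Either way the visits already exist.

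**The case against.** The strongest reply is that pain is only an example. The aim concerns adverse events in general, the record accepts any event, and a between-group comparison is planned. A journal article also condenses the full protocol, and the fields of the case record form are not shown.

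Much of this stands. A reader might infer that the feasibility aim cannot be answered at all. The documents do not support that: spasticity is well measured, events and delivered dose are recorded, and the comparison is stated.

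Two other strong readings also fail.

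- A reader might infer that scheduling problems are added to bodily harms in one count. The article only lists them as examples of what is recorded. Entries can be classified by type later, and scheduling is itself relevant to feasibility.
- A reader might infer that harm rates in the intensive arm will be diluted because its patients "receive one or two Lokomat trainings per day on 3-5 days per week". No per-training rate is planned. Intervention patients may train once a day, and the Abstract gives both arms the same weekly range of sessions.

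The condensation argument does not remove the remaining point. The article lists its instruments closely, down to the joints scored for spasticity, yet gives a measure to only one of the two harms it names. That is a mismatch between a stated aim and a stated list of data, and an analysis plan could not make it good.

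**Conclusion.** The point holds in a limited form. Pain is named as a harm of interest and has no dedicated measure with a baseline, a grade or a six-month value. The pain part of the secondary aim is weakly supported, and the rest of the aim is not affected.

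The gap is minor. It touches neither the primary outcome nor the sample size. No bias can be quantified, because the article gives no expected frequency or severity of pain.

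The conclusion assumes that the published list is complete as to instruments. If the full protocol or the case record form already carries a scheduled pain item, the remedy is only to name it in the Outcome section.

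**What to change.** Add a brief patient-reported pain rating (0-10) at baseline, bi-weekly during training and at six months. These are the times already set for the modified Ashworth and Penn scales, so both arms are asked equally often however many trainings they have per day. Compare change from baseline between the randomised groups. The open event record can stay as it is, as a supplement.

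Report the result as an estimated difference with a confidence interval. With 23 per group, 80% power is reached only for a difference of about 0.84 SD, so a non-significant result would not show that pain is unaffected.

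The cost is one question per existing assessment visit (six per patient if bi-weekly means every two weeks), with no extra visit or staff.

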## Methods/Design

The design of the study was developed in accordance with the Consolidated Standards of Reporting Trials (CONSORT statement)[16].

This study will take place at multiple sites (i.e. Zurich/CH (leading center), Barcelona/E, Toledo/E, Heidelberg/D, Murnau/D, Nijmegen/NL and Glasgow/GBR). Local Ethics Committees at each center have approved (Barcelona, Toledo and Zurich) the study. Informed consent will be obtained from all subjects prior to participation. Patients will be included as they are referred to one of the participating centers (consecutive sample).

### Subjects

Patients with a subacute traumatic SCI initially categorized as ASIA B or C with a motor level between C4 and T12 and who are only partially able to walk (Walking Index for Spinal Cord Injury-WISCI ≤5 [17]) will be eligible. Subjects should be able to start the training within 60 days after trauma. Patients who do not comply to the requirements of the Lokomat training device (i.e. bodyweight >130 kg, body height >200 cm, leg length diff >2 cm, osteoporosis, instable fracture of lower extremity, restricted range of motion, decubitus ulcer of lower extremity) or with concomitant injury limiting walking ability (e.g. lower extremity fractures, instable spine fractures, Joint instability preventing weight-bearing, severe soft tissue lesion, traumatic brain injury) or with pre-existing medical conditions interfering with unrestricted walking (e.g. total joint replacement, chronic pain, osteoarthritis, polyneuropathy, cardiopulmonary disease) or who are older than 60 years or younger than 18 years will be excluded from participation. Patients who already participate in other rehabilitation or pharmacological study will also not be considered for participation.

In previous studies with stroke subjects [18-23] the mean difference in walking speed amounted to 0.0418 m/s. This value was used to calculate the sample size further assuming a standard deviation of 0.05 m/s, a statistical power of 0.8 and a significance level of 0.05. The calculation resulted in the requirement of 23 subjects in each group to be able to reject the null hypothesis.

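### The stated 0.8 power rests on an unsourced SD of 0.05 m/s that is implausibly small for a cohort in which some patients will not walk

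*Protocol article*

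**What the plan says.** The sample-size paragraph (Protocol article, Methods/Design, Subjects) reports that in earlier stroke studies "the mean difference in walking speed amounted to 0.0418 m/s". It continues: "This value was used to calculate the sample size further assuming a standard deviation of 0.05 m/s, a statistical power of 0.8", with significance set at 0.05, and concludes: "The calculation resulted in the requirement of 23 subjects in each group". No source or population is given for the SD, and sidedness is not stated.

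The same section makes traumatic SCI patients eligible if initially ASIA B or C, with WISCI of 5 or less. The Outcome section names self-selected speed on the Ten Meter Walking Test as primary.

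On prognosis, the Background says that for ASIA B "the chance to become ambulatory is 50"%. It gives 95% for ASIA D, no figure for ASIA C, and no time point. The Abstract adds that "during the first 3 months most of the patients are not able to walk unsupported".

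No expected overground speed is given. The only speeds in the article are device settings (Intervention): "The walking speed will be set within the range of 1.6 to 3.1 km/h".

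**The concern.** When some patients cannot walk and others can, the spread of walking speed comes largely from the gap between the two sets of patients. That gap alone can exceed 0.05 m/s at quite slow walking speeds. The SD was neither taken from SCI patients nor visibly checked against this feature of the cohort.

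The stake is how the result is read. With a stated power of 0.8 for 0.0418 m/s, a non-significant comparison invites the conclusion that longer training brings no gain of that size. If the SD is really 0.10 m/s or more, the trial would miss such a gain most of the time.

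**Working it through.** **1. Reproducing the plan's figure.** Inputs from Subjects: difference 0.0418 m/s, SD 0.05 m/s, power 0.8, significance level 0.05. Equal groups are inferred from the stated group sizes.

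n per group = 2 × (1.960 + 0.842)² × (0.05 / 0.0418)² = 22.46 with unrounded quantiles, rounded up to 23.

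This is the two-sided normal approximation; a one-sided calculation gives 18. The exact t-test needs 23.46 (24) and has power 0.792 at 23. The arithmetic is sound, so only the SD is in question.

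**2. Lower bound on the SD.** Let p be the share walking, m the walkers' mean speed and s the SD among walkers. Assume that non-walkers score 0 m/s. Then

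SD = √(p·s² + p(1−p)·m²) ≥ m·√(p(1−p)).

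Setting the bound to 0.05 gives the highest walkers' mean compatible with the plan:

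| Split (either way round) | √(p(1−p)) | Largest m for SD 0.05 |
|---|---|---|
| 50/50 | 0.500 | 0.05/0.500 = 0.10 m/s |
| 25/75 | 0.433 | 0.05/0.433 = 0.115 m/s |
| 10/90 | 0.300 | 0.05/0.300 = 0.17 m/s |
| 5/95 | 0.218 | 0.05/0.218 = 0.23 m/s |

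A mean of 0.10 m/s corresponds to 100 s for 10 m. Any spread among walkers lowers these limits.

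**3. Power at 23 per group.** Noncentral t with 44 degrees of freedom, two-sided 0.05, noncentrality (0.0418/SD)·√(23/2):

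| SD (m/s) | 0.0418/SD | Power |
|---|---|---|
| 0.05 | 0.836 | 79% |
| 0.06 | 0.697 | 64% |
| 0.075 | 0.557 | 46% |
| 0.10 | 0.418 | 28% |
| 0.15 | 0.279 | 15% |

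**4. Sensitivity to the walking share.** This takes assumed walker means and no spread among walkers, the most favourable case:

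| Split | m = 0.20 m/s | m = 0.30 m/s |
|---|---|---|
| 50/50 | SD ≥ 0.10, power 28% | SD ≥ 0.15, power 15% |
| 25/75 | SD ≥ 0.087, power 36% | SD ≥ 0.13, power 19% |
| 10/90 | SD ≥ 0.06, power 64% | SD ≥ 0.09, power 34% |

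**5. The non-parametric option.** The Analyses section allows a non-parametric test instead. A simulation took 50% zeros, a walker SD of 20% of the control walkers' mean, and a walker shift of 0.0836 m/s (0.5 × 0.0836 = 0.0418 overall). With control walkers at 0.20 m/s, power was 18% for the t-test and 27% for Mann-Whitney. At 0.44 m/s (1.6 km/h ÷ 3.6, the lowest device speed, used only as an assumption) it was 8% and 10%. The rank test does not restore 80%.

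**6. Detectable difference.** At 23 per group, 80% power needs 0.845 SD: 0.845 × 0.10 = 0.08 m/s, 0.845 × 0.15 = 0.13 m/s, 0.845 × 0.25 = 0.21 m/s.

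**The case against.** The strongest reply is that the article does not rule out an SD of 0.05 m/s. It gives no overground speed for walkers and does not say how non-walkers are scored, which may be left to an analysis plan. The device speeds are set under guidance and body-weight unloading and do not predict self-selected overground speed. All of this stands, so the walker speeds and the zero score above are assumptions.

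Three stronger readings are tempting, and the document does not support them:

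- **About half the cohort will stay non-ambulatory.** The 50% is for ASIA B only, with no time point. ASIA C patients are also enrolled, and the Background says that patients with preserved algesia recover about as well as motor incomplete patients. Being unable to walk unsupported is also not the same as being unable to walk with aids or help.
- **Every walker would have to be at 0.10 m/s or slower.** The bound applies to the walkers' mean. With half at zero, walkers averaging 0.06 m/s with SD 0.057 m/s give √(0.5 × 0.0032 + 0.25 × 0.0036) = 0.05, and some of them can exceed 0.10 m/s.
- **The 23 per group is deficient because no allowance for loss is stated.** A journal article commonly leaves that to the full protocol.

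There is also a corner case in the plan's favour: 5% non-walkers and walkers at 0.20 m/s with no spread give 89% power. But that gives a B/C cohort the 95% prognosis that the Background reserves for ASIA D, and it needs near-identical speeds. At the other extreme, with 10% walking, SD 0.05 allows a group mean of only about 0.10 × 0.167 = 0.017 m/s, so a 0.0418 m/s difference would itself be hard to reach.

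**Conclusion.** The concern holds in conditional form. The SD of 0.05 m/s has no source, is paired with a difference from another disease, and is implausibly small for ASIA B/C patients with WISCI of 5 or less. The 0.8 power for 0.0418 m/s is therefore not supported.

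The conclusion does not depend on a half-and-half split. For non-walking shares from 10% to 90% and walkers averaging 0.20 m/s or more, power is at most 64%, even with no spread among walkers. An SD only 20% larger than planned (0.06 m/s) already gives 64%. These figures assume that non-walkers score 0 m/s, a true difference of 0.0418 m/s and 23 evaluable patients per group.

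A reader might infer that an SD of 0.05 m/s is impossible or that the calculation is wrong. Neither follows: the SD can hold under narrow conditions, and 23 reproduces.

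**What to change.** Keep 23 per group and revise the sample-size paragraph:

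- Withdraw the statement that this number gives 0.8 power for 0.0418 m/s.
- State that 23 evaluable patients per group detect about 0.845 SD with 80% power, and tabulate it: about 0.08 m/s at SD 0.10, 0.13 m/s at SD 0.15 and 0.21 m/s at SD 0.25.
- Base the SD on subacute ASIA B/C patients, with non-walkers counted as 0 m/s, and say so.
- Commit to interpreting a non-significant result through the confidence interval for the difference, not as evidence of no effect.

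The cost is rewording and a search for a suitable SD. No extra patients are needed. The downside is that the stated power becomes less favourable.
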